#### fNIRS data analysis

2.14.2

The fNIRS data will be processed and analyzed using the MATLAB 2020b software.

In lines with prior fNIRS studies investigating acupuncture (Qu et al., 2022; Si et al., 2021), fNIRS data preprocessing will be implemented using the Homer2 toolbox, which mainly including: (1) noisy channels will be rejected if any of the following criteria are met: the optical intensity (OI) falls outside the range of 0.5–1,000, the source-detector separation deviates over the range from the 0–45 mm (Broscheid et al., 2022), or the ratio between the mean optical intensity and its standard deviation [mean(OI)/std.(OI)] is less than 2; (2) at the participant level, if over 50% of a participant’s total channels are flagged as noisy, the entire dataset of this participant will be discarded due to insufficient signal quality; (3) the raw NIRS light intensity will be converted to an optical density (OD) signal; (4) the function hmrMotionArtifactByChannel will be used to identify motion artifacts; (5) then the motion correction will be conducted with the spline interpolation algorithm implemented in the function hmrMotioncorrectionSpline; (6) the interference of physiological noises will be reduced using a 0.01–0.2 Hz bandpass filter; and (7) the filtered OD data will be converted into the concentrations of HbO based on the modified Beer–Lambert law. Then, the hemodynamic response function will be estimated by a general linear model approach that uses ordinary least squares to get an average response for each of 20 CHs in every participant. Brain activation analysis will be conducted, and based on Montreal Neurological Institute (MNI) coordinates, CHs covering PFC and S1 will be predefined as the ROIs for subsequent functional connectivity analysis.

Given that the first fNIRS session includes both resting-state and task-state (cowhage-induced itch with VA or SA intervention, or WT control) scanning, while the 2−/4-Week-4 sessions only include resting-state scanning, these data will be analyzed separately according to different physiological states. Specifically, for the immediate effect of acupuncture antipruritus, the task-induced hemodynamic change (ΔHbO = task-state minus resting-state) during the first fNIRS scan will be calculated for each group. Since this is a single time-point measurement, the comparison (VA vs. SA vs. WT) of theseΔHbO values will be performed using one-way ANOVA. For the long-term effect of acupuncture antipruritus, only resting-state fNIRS data will be acquired at three time points (0−/2−/4-week). To account for the repeated-measures design across the three time points, LMM will be applied to longitudinal hemodynamic responses, with time, group, and their interaction as fixed effects, and a random intercept for each participant. The resting-state outcome measures will comprise: (1) regional HbO activity, defined as the temporal mean of the HbO concentration over the resting-state period for each channel; and (2) HbO-based functional connectivity, calculated as Fisher’s Z-transformed Pearson correlation coefficients between the time series of all channel pairs within and across the PFC and S1. The significance threshold is set to *p* < 0.05, and FDR correction will be strictly applied to control for multiple comparisons.

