### Core neuroimaging indicator: fNIRS data acquisition

2.11

Based on the efficacy of acupuncture for UP, this study will further focus on its central mechanism. According to previous studies (Mochizuki and Kakigi, 2015; Sun, 2025), we hypothesize that acupuncture’s antipruritic effect of UP correlates with modulation of cortical regions involved in itch processing, particularly the prefrontal cortex (PFC) and primary somatosensory cortex (S1), which can be captured in real-time by portable fNIRS. Moreover, considering that the oxyhemoglobin (HbO) signal has a better signal-to-noise ratio and is more reliable and sensitive than the deoxyhemoglobin signal (Strangman et al., 2002; Dravida et al., 2018), this trial will use cortical HbO changes to characterize the functional activity of PFC and S1, two regions of interest (ROIs). Therefore, the HbO change of task-state scanning data during the first fNIRS scan will be the primary outcome of the immediate effect of acupuncture on relieving itch, and the resting-state scanning data after 0−/2−/4-week interventions will be the primary mechanistic outcome of acupuncture’s long-term effect on UP.

Patients will undergo three fNIRS recording sessions. Each fNIRS scan will be scheduled on non-dialysis days or before dialysis sessions to minimize the influence of acute biochemical fluctuations. The first fNIRS scan will be conducted before the long-term acupuncture treatment, including an 8 min rest scanning and a 5 min task scanning during acupuncture treatment with immediate itch induction by the cowhage test (Figure 2A). Another two fNIRS scans will be performed after the 6th and 12th long-term acupuncture treatments, with only the 8 min rest scanning.

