**Figure 2 fig2:**
[figure not shown]
fNIRS data acquisition. **(A)** fNIRS scanning process diagram; **(B)** fNIRS channels location.

A portable fNIRS instrument (LIGHTNIRS, Shimadzu Corporation, Japan) will be utilized to measure cortical hemodynamic response, with a sampling rate of 13.33 Hz at wavelengths 780 nm and 830 nm. Due to PFC and S1 being ROIs of the mechanism hypothesis in this study, the optodes of fNIRS will be positioned over the prefrontal and bilateral primary somatosensory cortex. The fNIRS cap is created by 8 × 2 light sources and detectors (20 channels) placed according to the international 10–20 EEG system, with a separation distance of 2.5–3 cm for all optodes (Figure 2B). To achieve precise spatial registration, the Montreal Neurological Institute coordinates of all optodes will be measured using an electromagnetic 3D digitizer system, and the corresponding brain regions of the midpoint of each channel in the Brodmann Talairach template will be calculated.

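### The 50% noisy-channel rule discards a participant's whole fNIRS dataset without saying over which recordings channels are counted, so usable scans can be lost needlessly

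*Protocol article*

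**What the plan says.** Step (2) of the preprocessing list in section 2.14.2 sets an exclusion rule "at the participant level": "if over 50% of a participant’s total channels are flagged as noisy", then "the entire dataset of this participant will be discarded due to insufficient signal quality". Step (1) has already rejected each noisy channel by numeric criteria. No text provides for keeping a participant's good recordings when another fails.

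Section 2.11 sets out the recordings. "Patients will undergo three fNIRS recording sessions". The first takes place before the long-term treatment, "including an 8 min rest scanning and a 5 min task scanning during acupuncture treatment". For the rest, "Another two fNIRS scans will be performed after the 6th and 12th long-term acupuncture treatments, with only the 8 min rest scanning". The cap has 20 channels.

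The same section names two primary mechanistic outcomes: the HbO change in the task scan for the immediate effect, and the resting-state data at 0, 2 and 4 weeks for the long-term effect. Section 2.14.2 analyses them separately. The immediate effect is a one-way ANOVA on ΔHbO (task minus rest, first session). For the long-term effect, "LMM will be applied to longitudinal hemodynamic responses", with a random intercept per participant.

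**The concern.** The rule works on whole participants, but the analyses work on recordings. The ANOVA uses only the first session. A likelihood-based mixed model can use a participant who has one or two of the three resting scans. Neither analysis needs a participant's good recordings deleted because another recording is poor.

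Two things are at stake. The first is avoidable loss of data from one or both mechanistic primary outcomes. The second is the make-up of the week-0 comparison. If a noisy scan at week 2 or 4 can remove the week-0 task scan, the immediate-effect analysis is conditioned on something observed after randomisation and after weeks of treatment or waiting. If signal quality at those visits differed by arm, for instance because patients who itch more move more, the arms compared at week 0 would no longer be the arms as randomised.

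The missing unit also leaves analysts free to choose how to count once they have seen which scans are noisy.

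**Working it through.** **Inputs from the article.** 20 channels; three sessions; one task scan, in session 1 (section 2.11); 32 enrolled per arm (section 2.5). The article has no figure for fNIRS scan loss to reproduce. The 32 does reproduce: 27 / (1 − 0.15) = 31.8, rounded up to 32, and 3 × 32 = 96. It is used here only as the number of participants per arm.

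**Assumed.** A failure probability p per session, independent across the three sessions. The article gives no failure rate, so p = 5% and 10% are illustrations.

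**Step 1: what each count does.**

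- *Per scan (out of 20).* One bad scan triggers the rule. A bad week-4 scan removes good scans at weeks 0 and 2, including the task scan.
- *Pooled over three sessions (out of 60).* One wholly bad scan is 20/60 = 33% and removes nothing. Two are 40/60 = 67% and remove the third. If they fall at weeks 2 and 4, the good task scan is lost.
- *First session only.* A bad first session removes good resting scans at weeks 2 and 4. The task scan would be lost or kept on its own quality, so the immediate analysis does not depend on later visits.

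All three counts can discard usable recordings. The first two can make week-0 inclusion depend on later scans.

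**Step 2: task scans lost because of the rule, per-scan counting.** ΔHbO needs session 1, so a failed session 1 loses it under any rule. The loss due to the rule is a good session 1 with at least one bad later session: (1 − p)[1 − (1 − p)²].

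- p = 5%: 0.95 × (1 − 0.9025) = 0.0926, or 9.3%; × 32 = 3.0 per arm.
- p = 10%: 0.90 × (1 − 0.81) = 0.171, or 17.1%; × 32 = 5.5 per arm.

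Check against expected task scans kept per arm, 32(1 − p)³ under the rule and 32(1 − p) if only the failing scan is dropped:

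- p = 5%: 27.4 against 30.4.
- p = 10%: 23.3 against 28.8.

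The differences agree with the figures above.

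**Step 3: the same under pooled counting, with sessions wholly good or wholly bad.** Both later sessions must fail: (1 − p)p².

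- p = 5%: 0.95 × 0.0025 = 0.24%; × 32 = 0.08 per arm.
- p = 10%: 0.90 × 0.01 = 0.9%; × 32 = 0.29 per arm.

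The chance that a participant loses all fNIRS data, 3p²(1 − p) + p³, is 0.7% and 2.8%. Under per-scan counting, 1 − (1 − p)³ gives 14.3% and 27.1%.

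**Step 4: dependence.** Independence makes the per-scan loss large. If the same patients tend to fail at every session, the total loss falls from 1 − (1 − p)³ towards p, and the part caused by the rule falls towards zero.

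**The case against.** The strongest reply is that the article never says one bad scan is enough. The trigger refers to a participant's total channels, and under pooled counting a single wholly bad scan removes nothing. The article is a condensed account, its preprocessing list is introduced as covering the main steps, and task and rest data are analysed separately, so quality control may in practice run per recording. The failure rates are assumed.

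Much of this stands. A reader might infer that any single bad scan deletes the participant, but that follows only under per-scan counting, or when the first session is the bad one and decides the matter. The article does not settle which applies. It does not stand as a full answer, however, because the consequence is stated: the whole participant dataset goes. Reading that as one recording goes against the words, and the other counts also lose good scans. This is a stated rule that is badly fixed, not detail left out.

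Three further inferences are tempting and not supported:

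- *That the randomised comparison is undermined.* This needs later signal quality to be related to arm or outcome, and the article gives no evidence of it. The noise criteria are numeric and the same in every group.
- *That the loss erodes the 27 per arm.* That number powers the 24 h-WI-NRS (section 2.5). The rule sits in the fNIRS section and does not reach the clinical intention-to-treat analysis in section 2.14.1. No fNIRS power target is stated.
- *That each region of interest needs its own channel threshold.* The resting outcomes are defined per channel and per channel pair, and step (1) already drops noisy channels. The number of S1 channels is not in the text available. A regional threshold could itself discard valid channels.

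**Conclusion.** The point holds in this form: the rule is set per participant, leaves the counting unit undefined, and on each of the three plausible counts can discard usable recordings that the ANOVA and the mixed model do not need to lose. Under per-scan and pooled counting it can also tie week-0 inclusion to later signal quality, which is a possible source of bias that the documents neither show nor exclude.

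The size cannot be fixed from the article. It ranges from under 1% of task scans (pooled counting, p up to 10%) to 9.3% or 17.1% (per-scan counting, p = 5% or 10%), given independent failures. First-session counting costs no extra task scans but does cost later resting scans. The matter is confined to the mechanistic fNIRS outcomes. It merits a correction before the data are processed, mainly because the correction is nearly free.

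**What to change.** Reword step (2) of section 2.14.2 to say that:

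- the 50% threshold is applied to each recording separately, with session-1 rest and session-1 task counted as two recordings;
- only the recording that fails is dropped;
- the participant's remaining resting scans stay in the mixed model;
- inclusion in the ΔHbO analysis depends only on the session-1 rest and task recordings, whatever the later scans look like.

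No threshold by region of interest is needed. The cost is one or two sentences and a small change to the preprocessing script, with no extra data. The wording should be settled before any scan is screened for noise.

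### No named step lets the trial tell a cortical HbO change from a systemic one: the band-pass keeps oscillations near 0.1 Hz, there is no short channel, and HbR is not used

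*Protocol article*

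**What the plan says.** Section 2.11 states that "this trial will use cortical HbO changes to characterize the functional activity of PFC and S1". It makes task-state HbO change the primary outcome for the immediate effect, and says that the resting-state data "will be the primary mechanistic outcome of acupuncture’s long-term effect on UP". The device records "with a sampling rate of 13.33 Hz at wavelengths 780 nm and 830 nm", and the cap has 20 channels "with a separation distance of 2.5–3 cm for all optodes".

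Section 2.14.2 lists seven preprocessing steps. The one aimed at physiology is that "the interference of physiological noises will be reduced using a 0.01–0.2 Hz bandpass filter". After it, "the filtered OD data will be converted into the concentrations of HbO based on the modified Beer–Lambert law", and "the hemodynamic response function will be estimated by a general linear model approach that uses ordinary least squares"; no systemic regressor is named. Resting-state connectivity is "calculated as Fisher’s Z-transformed Pearson correlation coefficients between the time series of all channel pairs within and across the PFC and S1". It goes into a linear mixed model with group, time and their interaction, with FDR correction.

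The limitations (section 3.4) cover uremic toxin fluctuation, the cowhage model and detection depth. They do not mention systemic or scalp blood flow. Section 3.3 calls fNIRS little affected by scalp conditions, but in a comparison with EEG electrode impedance and sweat, which is a different matter.

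**The concern.** An HbO channel 2.5–3 cm long sees scalp as well as cortex, and blood-pressure waves reach both. A 0.2 Hz upper edge removes the heartbeat (about 1 Hz) but not slow pressure waves, taken here as near 0.1 Hz. Correlating raw HbO series over all channel pairs then counts any shared systemic wave as connectivity. Short channels, a systemic regressor, HbR and common-component removal could each help to separate the two sources; none is named.

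What is at stake is the trial's main claim, a central mechanism. Only the VA arm has skin penetration, SA has blunt contact and WT has none, so systemic responses may differ by arm. Randomisation balances physiology at baseline but not a change that the treatment itself causes. FDR controls multiplicity and does not correct such a bias.

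**Working it through.** The plan gives no figure on this point to reproduce. Its sample size (27 per group) does reproduce and is used below only as n.

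**Inputs from the protocol.** Filter 0.01–0.2 Hz (order not stated); 13.33 Hz sampling; 8 min rest; 20 channels, so up to 20 × 19 / 2 = 190 pairs; 27 per group.

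**Assumptions.** Pressure waves near 0.1 Hz (range 0.08–0.15 Hz); a Butterworth filter run forward and backward, orders 2–4; systemic variance shares from 0.1 to 0.5.

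**Step 1: what the filter passes.** For edges f1 and f2 and order n, the zero-phase amplitude gain is 1 / (1 + q^(2n)), with q = (f² − f1·f2) / (f·(f2 − f1)).
- Planned band at f = 0.1: q = (0.01 − 0.002) / (0.1 × 0.19) = 0.421. Order 3: 1 / (1 + 0.421^6) = 0.99. Orders 2–4: 0.97–1.00.
- The same band gives 0.99–1.00 at 0.08 Hz, 0.92–0.99 at 0.12 Hz and 0.79–0.93 at 0.15 Hz. The result does not hang on exactly 0.1 Hz.
- Upper edge 0.08 Hz at f = 0.1: q = (0.01 − 0.0008) / (0.1 × 0.07) = 1.314. Order 3: 1 / (1 + 1.314^6) = 0.16.

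**Step 2: effect on connectivity.** Let each filtered channel be √(1 − s) × cortical signal + √s × shared systemic signal, all with unit variance, and let the true cortical correlation be ρ. Then r = (1 − s)ρ + s.
- With ρ = 0, r = s. Fisher Z is 0.10, 0.20, 0.31 and 0.55 for s = 0.1, 0.2, 0.3 and 0.5.
- Simulated 8-min records (order 3, shared signal at 0.08–0.12 Hz) gave 0.10, 0.21, 0.31 and 0.57 with the planned band, and 0.02, 0.03, 0.06 and 0.12 with a 0.08 Hz edge.
- With 1/f-type backgrounds and s defined on the unfiltered signal, shares of 10–40% gave r = 0.12–0.44 in one run and 0.18–0.56 in another. The size depends on the background; the direction does not.

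**Step 3: when an arm difference arises.** If s is the same in both arms, the difference in r is (1 − s) × (difference in ρ): a true difference shrinks, and no false one appears. A false one needs s to differ by arm. With ρ = 0 in both arms, and one pair tested by an unadjusted two-sided t test at 0.05 with 27 per group:

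| Shares | Shift in Z | Rejection probability, between-patient SD 0.2 | SD 0.3 |
|---|---|---|---|
| 0.2 vs 0.3 | 0.09 (simulated) | 0.33 | 0.19 |
| 0.2 vs 0.4 | 0.22 | 0.95 | 0.70 |

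The total SD adds a within-record SD of about 0.09: √(0.09² + 0.2²) = 0.22 and √(0.09² + 0.3²) = 0.31. The closed-form shift for the first row is 0.310 − 0.203 = 0.107, which gives 0.42 and 0.23. These are single-pair figures, not the plan's FDR-adjusted mixed model.

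**Step 4: limits of a narrower band.** With the shared signal at 0.02–0.06 Hz, moving the upper edge to 0.08 Hz raised spurious r from 0.16–0.56 to 0.22–0.65. The narrower band helps only against signal above its edge.

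Task ΔHbO was not simulated. The same reasoning applies to it in kind, but no size is given.

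**The case against.** **Equal systemic signal cancels.** With a sham arm, randomisation, a week-0 scan and a group-by-time test, systemic signal that is stable or common to the arms gives no false interaction. This stands. A reader might infer that any VA–SA connectivity difference is blood flow; the documents do not support that.

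**Resting scans are not taken during needling.** The later scans follow the 6th and 12th sessions, so connectivity would need a carry-over or lasting systemic change that differs by arm. The protocol offers no evidence of one. This stands and weakens the connectivity route. It does not touch task ΔHbO, which is recorded with needles in place, although manipulation is described only for the long-term sessions.

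**The sizes are built in.** With zero true coupling, r equals the assumed share, and the arm differences in share have no source. This stands: the figures show sensitivity and do not predict.

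**Silence is not exclusion.** The article presents its preprocessing list as the main steps, and a fuller plan may hold more. This stands in part: one cannot say that HbR or nuisance regression is ruled out. But the montage, the HbO-only outcome and the connectivity formula are fixed, and the stated limitations omit the issue.

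**HbO is a reasoned choice.** Section 2.11 justifies it by signal-to-noise, and scans are timed around dialysis. This supports HbO as the main measure. It does not argue against HbR as a check, and the scan timing is aimed at biochemistry.

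**Conclusion.** The concern holds as one of interpretation. The named pipeline passes a shared oscillation near 0.1 Hz almost intact (amplitude 0.97–1.00) and has no named means to separate it from cortical signal. Such a signal inflates HbO connectivity by s(1 − ρ). If treatment alters systemic physiology differently by arm, a group or group-by-time difference in connectivity or in task ΔHbO could be systemic. An arm gap in share of 10 points moves Z by about 0.1, and one of 20 points by about 0.22. These figures rest on an assumed frequency and assumed shares, and neither the gap nor its direction is known.

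A reader might also infer that the 0.2 Hz edge is an error to be replaced by 0.08 Hz, or that HbR agreement should be a condition for any claim. Neither follows. The lower edge can make slower systemic signal more prominent, and HbR is too noisy to act as a hard gate. The supportable conclusion is that the trial should be able to test a positive finding for systemic origin and, as described, it cannot.

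**What to change.** Keep HbO and the planned band as the primary analysis. Before the data are seen:

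1. Derive HbR from the same 780/830 nm recordings and pre-specify it as a supporting measure for ΔHbO and for connectivity.
2. Pre-specify two sensitivity analyses of connectivity: one with the all-channel common component removed (first principal component or channel mean), and one with a narrower band, for example an upper edge of 0.08 Hz.
3. State that an effect will be called cortical with confidence only if it is robust to these analyses; otherwise report that a systemic origin cannot be excluded.
4. Add systemic and scalp blood flow to the limitations in section 3.4.

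Cost: wording and extra processing, with no new hardware, visits or patients. Downsides: HbR is noisier than HbO. Removing the common component can also remove genuine signal shared by PFC and S1. The narrower band raises the SD of a single connectivity estimate from about 0.06–0.10 to 0.12–0.15 and leaves slower systemic signal in place. For these reasons they belong in support of the primary analysis and should not replace it.

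### The resting-state regional HbO measure averages a signal whose average the 0.01 Hz filter edge has already removed, so one of the two long-term mechanistic measures carries no information

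*Protocol article*

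**What the plan says.** Section 2.14.2 of the protocol article (fNIRS data analysis) sets out numbered preprocessing steps for the fNIRS data as a whole: "fNIRS data preprocessing will be implemented using the Homer2 toolbox". In step (6), "the interference of physiological noises will be reduced using a 0.01–0.2 Hz bandpass filter". In step (7), "the filtered OD data will be converted into the concentrations of HbO based on the modified Beer–Lambert law". HbO is thus computed from a signal that has already been filtered.

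The same section then lists two resting-state measures. The first is "regional HbO activity, defined as the temporal mean of the HbO concentration over the resting-state period for each channel". The second is functional connectivity, formed from Fisher-transformed correlations between channel pairs within and across PFC and S1. The longitudinal data at weeks 0, 2 and 4 go into a linear mixed model with group, time and their interaction.

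Section 2.11 says that the resting-state data "will be the primary mechanistic outcome of" the long-term effect. The first session is described as "including an 8 min rest scanning and a 5 min task scanning during acupuncture treatment", and the two later sessions are "with only the 8 min rest scanning".

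**The concern.** The filter and the outcome definition work against each other. The outcome asks for the average HbO over the scan, and the filter deletes exactly that average before HbO is computed. What remains to be averaged is a fluctuation around zero, so its mean reflects how the filter behaves at the ends of the record and not the state of the cortex.

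At stake is the only resting-state measure of regional activity. A non-significant group-by-time interaction could be read as evidence that acupuncture leaves resting PFC and S1 activity unchanged, although nothing about its level was measured. A significant channel could be read as a treatment effect when it is chance or artefact. Section 2.14.1 also plans correlations between fNIRS results and clinical outcomes, and any that use this variable would inherit the fault.

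**Working it through.** The plan states no figure on this point, so there is none to reproduce. The check has three parts.

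**Inputs from the document.** Filter band 0.01–0.2 Hz, applied before conversion to HbO (section 2.14.2). Rest scan of 8 min = 480 s (section 2.11). Acquisition "with a sampling rate of 13.33 Hz at wavelengths 780 nm and 830 nm" (section 2.11, under Figure 2). The lower edge of 0.01 Hz corresponds to a period of 1/0.01 = 100 s. The lowest non-zero frequency that a 480 s scan resolves is 1/480 = 0.0021 Hz, about a fifth of the lower edge.

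**Assumptions.** The filter type and order are not given, so they were varied. The modified Beer–Lambert step is taken as linear, so that zero-mean optical density gives zero-mean HbO. Simulated levels and noise are in arbitrary units.

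**1. Filter gain.** The temporal mean, (1/N) Σ x(t), is the 0 Hz component of the scan. Gain of a Butterworth band-pass of 0.01–0.2 Hz:

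| Order | Gain at 0 Hz | Gain at 1/480 Hz |
|---|---|---|
| 1 | 0 | 0.19 |
| 3 | 0 | 0.008 |
| 5 | 0 | 0.0003 |

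The gain at 0 Hz is zero for every order tried.

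**2. A constant level.** A constant of 1 over 480 s was passed through four filters. The mean of the output was at most 2 × 10⁻⁹ in absolute value. Because the filters are linear, a true level L contributes at most L × 2 × 10⁻⁹ to the measured mean.

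**3. Simulated scans.** For each filter, 500 scans of 480 s at 13.33 Hz were generated with a between-scan level SD of 3, a random linear drift (SD 1 over the scan) and 1/f noise with SD about 1.

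| Filter | SD of mean before | SD of mean after | After/before | Correlation of mean after with mean before | Largest absolute mean after |
|---|---|---|---|---|---|
| Zero-phase, high-pass order 5 + low-pass order 3 | 3.120 | 0.015 | 0.47% | -0.04 | 0.051 |
| Zero-phase band-pass, order 3 | 2.997 | 0.018 | 0.59% | 0.05 | 0.058 |
| Causal band-pass, order 3 | 3.072 | 0.008 | 0.28% | -0.10 | 0.035 |
| FFT band-pass | 3.035 | 0.000 | 0.00% | 0.01 | 0.000 |

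The within-scan SD after filtering was 0.54–0.64, so the fluctuations survive while the mean does not. The correlations are near zero, as part 2 implies: the residue is not a scaled-down copy of the level.

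Filtering the first session as a single record of 8 + 5 = 13 min does not rescue the resting mean. Its SD over 300 simulated sessions was 0.015 (first filter in the table).

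**The case against.** The strongest defence is that this is a condensed article. The preprocessing list is introduced as covering the main steps and so is not presented as complete. It leads into a general linear model for the haemodynamic response, which suits task data. The section then says that rest and task data will be analysed separately. A resting-state path without the high-pass could exist in a fuller document.

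That lowers certainty about what will finally be run, but it does not make the printed text consistent. The steps are stated for fNIRS data in general and in a fixed order, and the resting measure is explicitly a temporal mean, not a model coefficient. Nothing says that the mean comes from unfiltered data or that the level is restored. This is a conflict between two stated rules, not a detail left to another document.

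Other objections limit the point, and they stand. A reader might infer that a null result is guaranteed. It is not: a mixed model fitted to small residue would still reject at about its nominal rate before FDR correction. A reader might also infer that the trial can no longer test its PFC/S1 hypothesis over the longer term. The document does not support that either, because the resting-state data comprise two measures and connectivity, being a correlation, does not depend on the mean.

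**Conclusion.** The point holds. As written, the first resting-state measure is about zero plus edge residue for every patient and visit, and its between-scan SD is 0–0.6% of what it would be without the filter. The zero gain at 0 Hz carries the conclusion. The simulation only illustrates the size of the residue, and its units and noise levels are assumed, not taken from the trial. The conclusion would fail only if the resting mean were taken from data without the high-pass, which the text does not say.

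The damage is confined to one of the two listed measures of the long-term mechanistic outcome, and to correlations that use it. Connectivity, the 24 h-WI-NRS analysis, the VA versus SA comparison and the sample size are untouched. A reader might extend the fault to the immediate task-minus-rest HbO change. The article does not settle that, because it does not say whether the change is a difference of means from the filtered record or comes from the general linear model, so it is not claimed here.

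**What to change.** In section 2.14.2, before any analysis of the longitudinal scans, replace the temporal mean with a regional measure that survives the 0.01–0.2 Hz filter. The SD or amplitude of the filtered HbO over the rest period, per channel or per ROI, does so directly. If a fractional amplitude is preferred, compute it from data before the band-pass, because its denominator needs the wider spectrum. Keep the mixed model, the FDR correction and the connectivity measure as planned; the fault gives no reason to re-rank the outcomes.

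The cost is a change of wording and a few lines of MATLAB. Data collection and sample size stay the same. The one drawback is interpretive: the measure then describes the amplitude of low-frequency fluctuation, not the level of HbO, and must be labelled and discussed as such. The change should be dated before the data are examined, since a replacement chosen afterwards would be post hoc.
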